### Intervention

The intervention consists of supervised implementation of the guideline "*Oral health care in (residential) care homes for elderly people*" and the daily oral health care protocol derived from the guideline. In each institution of the intervention group, every ward head appoints a nurse who will act as ward oral health care organizer (WOO). The managing director, physician(s), ward heads, WOO's, nurses, nurse aides, and a sample of 30 residents are involved in the study. The implementation of the guideline is supervised by a dental hygienist and includes:

• A 1.5-hour informative oral presentation on the guideline, the daily oral health care protocol, and the supervised implementation project before the start of the study, introduced by the dental hygienist and one of the investigators and addressing the managing director, the institution study supervisor, the ward heads, and the WOO's. Important objective of the informative oral presentation is to lay a strong institutional foundation of the implementation project and the study.

• A 2-hour lecture and in total 3 hours of practical education for the WOO's. The education, presented by the dental hygienist, regards the theoretical and practical essentials of the guideline. The WOO's are practically educated in skills facilitating them to practically educate and encourage the nurses and nurse aides of theirs wards.

• A 1.5-hour theoretical and executive education session at each ward, presented by the WOO, for all ward nurses and nurse aides. This education session is scheduled after the baseline data collection. A summary of the guideline is presented and all executive actions, such as tooth brushing, are taught and demonstrated with ward residents on site. As from the education session, the WOO will encourage and assist the nurses and nurse aides regularly in the daily delivery of oral health care.

• Providing oral health care materials and products for each resident by the dental hygienist.

• Monitoring visits of the dental hygienist and an investigator every 6 weeks, meeting the institution study supervisor and WOO's for listing and resolving implementation and study problems.

### Data collection

Research data are gathered in the institutions of the intervention and the control group. At baseline, a questionnaire on the resident capacity of the institution, the mean length of stay of the entire group of residents, mean age of the entire group of residents, and the presence of oral health care providers is completed by the managing director of each institution. At baseline and at 6 months, an oral examination of the random sample of 30 residents is carried out by a team of trained external examiners (dentists, master dental students, and master dental hygiene students). They will carry out the data collection after exercising and calibrating the examination criteria and after determining their intra- and inter-examiners' reliability in a pilot study. The examiners do not know whether an institution is allocated to the intervention or the control group. At baseline, a questionnaire on personal and medical details of every resident of the random sample is completed. Furthermore, at baseline and at 6 months a questionnaire addressing the nurses and nurse aides is completed. Finally, at the end of the study, a process evaluation is conducted in the institutions of the intervention group to acquire insight in the stimulating and inhibiting factors of the implementation process. Figure 1 presents a flowchart of the study protocol and Table 1 presents an overview of the data collection.

**Table 1 T1:** Overview of data collection

Data	Collection time	Purpose
**Institution questionnaire ** resident capacity mean length of stay of residents mean age of residents presence of oral health care providers	baseline baseline baseline baseline	comparison institutions comparison institutions comparison institutions comparison institutions

**Nurses and nurse aides questionnaire** gender age years of experience oral health knowledge attitude to personal oral health care	baseline/6 months baseline/6 months baseline/6 months baseline/6 months baseline/6 months	comparison nurses and nurse aides comparison nurses and nurse aides comparison nurses and nurse aides intervention effect intervention effect

**Resident questionnaire**		
Age	baseline	comparison residents
Gender	baseline	comparison residents
Primary diagnoses	baseline	comparison residents
secondary diagnoses	baseline	comparison residents
prescribed drugs	baseline	comparison residents
Care Dependency Scale	baseline	comparison residents
Mini Mental State Examination	baseline	comparison residents

**Oral examination** Plaque index (natural teeth, denture)	baseline/6 months	intervention effect

**Figure 1 F1:**
[figure not shown]
**Flowchart of the study protocol**.

#### Oral examination

The oral hygiene level of natural teeth is assessed using the validated plaque index described by Silness and Löe (score range 0-3) at a subset of the so-called 'Ramfjörd teeth' [50]. In absence of one of these teeth, the corresponding distal neighbour tooth will be assessed. The oral hygiene level of dentures is assessed using a Methylene Blue^® ^denture plaque disclosing solution according to the method of Augsburger and Elahi (score range 0-4) [51].

#### Resident questionnaire

The resident questionnaire is completed by a physician of the institution and records personal details, primary diagnosis, secondary diagnoses, Care Dependency Scale (CDS) score [52], Mini Mental State Examination (MMSE) score [53], and prescribed drugs.

#### Nurse and nurse aide questionnaire

The self-administered validated questionnaire addressing the nurses and nurse aides covers personal details, years of experience, oral health knowledge, and attitude to personal oral health care.

#### Process evaluation

During monitoring visits of the dental hygienist and an investigator every 6 weeks during the intervention, meeting the institution study supervisor and WOO's, problems of the implementation project and the study are listed and resolved. At 12 and 24 weeks, a SWOT analysis is performed. SWOT is a strategic planning method for evaluating the Strengths, Weaknesses, Opportunities and Threats, identifying the favourable and unfavourable factors while achieving the implementation project objectives. A 10 items questionnaire is used concerning the progress, the involvement of the residents, and the organizational aspects of the implementation project. At the end of the study, the implementation project is evaluated by an in-depth, face-to-face, semi-structured interview with a random sample of nurses and nurse aides of each institution. Main questions of the semi-structured interview are on observed alterations of the oral health care provided in the institution, causality of these alterations and difficulties experienced during the implementation process. Subsequently, an adaptation of 'reflective listening' is used, a counselling technique eliciting a thorough disclosure of thoughts and feelings [54]. The technique involves reflecting what the interviewer believes was said in order to verify or clarify the nurses' and nurse aides' statements. Using this technique, the nurses and nurse aides are also actively confronted with eventual inconsistencies in their answers and statements. The interviews take 20-30 minutes and are conducted individually by the two investigators. All interviews are taped and transcribed.

### Statistical analysis

Both categorical and continuous variables are initially analyzed using exploratory data analysis, employing a variety of mostly graphical techniques and techniques for testing the necessary assumptions. The institution is the unit of randomization and the residents are the units of analysis. Cluster effects are addressed in the analysis. Intraclass correlation will be calculated for each outcome variable as a measure of correlation among residents within the institutions as well as among institutions within each country. The effect of the implementation project at individual, institution and country level is summarized and analyzed in a multilevel comparative analysis. Three comparative dimensions are handled simultaneously: the resident effect, the institution effect, and the country effect. Therefore, a three-level structure is used with resident (level 1) and institution (level 2), nested in broader organization units on country level (level 3). Differences in primary outcomes at baseline and differences between the intervention and the control group as well as between countries at baseline and at 6 month are calculated. Covariates at individual level are the subjects of the resident questionnaire and the nurse and nurse aide questionnaire.

Responses to the semi-structured interview of the process evaluation are analyzed using coding techniques commonly utilized for qualitative research methods [55]. Recurrent themes in the responses are used to set up a framework.

All research data are analyzed using MANOVA. A multilevel regression analysis is performed to determine the most important predicting factors with respect to oral hygiene level.

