### Aim and objectives

The overall aim of the study is to compare a supervised versus a non-supervised implementation of the guideline "*Oral health care in (residential) care homes for elderly people"*. The aim can be rendered into 5 research questions:

1. Is there any statistically significant difference between oral hygiene levels of elderly residents in (residential) care homes with supervised implementation of the guideline when compared to those in (residential) care homes without supervised implementation of the guideline?

2. Is there at care home level any statistically significant difference between attitude and knowledge level of nurses and nurse aides of (residential) care homes with supervised implementation of the guideline when compared to those in (residential) care homes without supervised implementation of the guideline?

3. Is there any statistically significant difference in impact on the outcome variables of research questions 1 and 2 between the (residential) care homes in The Netherlands when compared to Flanders (Belgium) and which factors are causing the country differences?

4. Which factors are stimulating or inhibiting the implementation of the guideline in the (residential) care homes in The Netherlands and Flanders (Belgium)?

5. What is the compliance of and which barriers are perceived by the nurses and nurse aides in (residential) care homes in The Netherlands and Flanders (Belgium) while implementing the guideline?

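### Staff knowledge and attitude are outcomes compared between care homes, but the stated analysis has residents as its units and no level for staff

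*Protocol article*

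**What the plan says.** Research question 2, under Aim and objectives, reads "Is there at care home level any statistically significant difference between attitude and knowledge level of nurses and nurse aides" and goes on to contrast supervised with non-supervised homes. Research question 3 asks for a country comparison on the outcomes of questions 1 and 2, so it uses the staff outcomes again.

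Table 1, under Data collection, lists oral health knowledge and attitude to personal oral health care within the nurse questionnaire. Both are collected at baseline and 6 months, and the purpose of both is to show the effect of the intervention. The section on the questionnaire says who answers it: "The self-administered validated questionnaire addressing the nurses and nurse aides covers personal details". The Discussion names better staff knowledge and attitude as an essential aim of the project.

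The Statistical analysis section says:

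- "The institution is the unit of randomization and the residents are the units of analysis".
- "Intraclass correlation will be calculated for each outcome variable as a measure of correlation among residents within the institutions", and also among institutions within each country.
- The multilevel model has resident at level 1, institution at level 2 and country at level 3.
- "Covariates at individual level are the subjects of the resident questionnaire and the nurse and nurse aide questionnaire".
- All research data are analysed by MANOVA.
- A multilevel regression looks for predictors, with oral hygiene level as the only response named.

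**The concern.** The staff scores are outcomes compared at home level in one part of the article. In the analysis section the stated units are residents, and the staff questionnaire appears only as a source of covariates. Staff are not nested in residents, and nothing in the article links a particular nurse to a particular resident. A staff score therefore has no natural row, as a response or as an individual-level covariate, in a model whose only individuals are residents. Likewise, a correlation among residents says nothing about how alike the staff of one home are.

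At stake is the validity of the test for research question 2, and for the part of question 3 that reuses its outcomes. Staff of one home share managers, training and, in the intervention arm, the same education sessions. A test that treats them as independent overstates the evidence.

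**Working it through.** **Step 1. Compare the statements.** The article gives no figure for the staff outcomes, so there is none to reproduce.

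| Item | Aims and Table 1 | Statistical analysis |
|---|---|---|
| Role of knowledge and attitude | Outcomes | Nurse questionnaire listed with covariates |
| Who is measured | Nurses and nurse aides | Residents are the units |
| Level of comparison | Care home | Resident, institution, country |
| Intraclass correlation | Not applicable | Among residents, for each outcome |

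The multilevel model has no staff level. The further multilevel regression has oral hygiene as its response. That leaves MANOVA as the only stated analysis that can take staff scores as responses, and its unit and its handling of staff clustering are not stated.

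**Step 2. Size of the problem if staff are analysed individually without cluster adjustment.**

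Inputs:
- Significance level 0.05 (Participants and setting); two-sided is assumed.
- Design effect formula from the same section: Deff = 1 + (m − 1)ρ, with m now the number of staff per home.
- m = 10 to 30 and staff ρ = 0.05 to 0.10 are assumptions. The article's ρ of 0.95 belongs to the sample size for plaque among residents and is not carried over.

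With equal numbers per home and a large-sample approximation, ignoring clustering understates the variance of the arm difference by the factor Deff. The actual type I error is then 2 × [1 − Φ(1.96/√Deff)].

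| Staff per home | ρ | Deff | 1.96/√Deff | Type I error |
|---|---|---|---|---|
| 10 | 0.05 | 1 + 9 × 0.05 = 1.45 | 1.63 | 0.104 |
| 20 | 0.05 | 1 + 19 × 0.05 = 1.95 | 1.40 | 0.160 |
| 30 | 0.05 | 1 + 29 × 0.05 = 2.45 | 1.25 | 0.211 |
| 10 | 0.10 | 1 + 9 × 0.10 = 1.90 | 1.42 | 0.155 |
| 20 | 0.10 | 1 + 19 × 0.10 = 2.90 | 1.15 | 0.250 |
| 30 | 0.10 | 1 + 29 × 0.10 = 3.90 | 0.99 | 0.321 |

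Over the same range of staff numbers, the error is 0.06 to 0.08 at ρ = 0.01 and 0.24 to 0.45 at ρ = 0.20.

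**Step 3. What a home-level test rests on.** There are 24 homes. A plain two-group comparison of home means has 24 − 2 = 22 degrees of freedom, with a critical t of 2.07. Within one country there are 12 homes and 10 degrees of freedom, with a critical t of 2.23.

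**The case against.** The best defence is that the unit sentence and the three-level model were written for plaque. The sentence does not say that it covers every outcome, the same paragraph speaks of primary outcomes, and research question 2 fixes its own level. The Discussion mentions explanatory variables at resident, institution and country level, which leaves room for staff data to enter at home level. The section also says that cluster effects are addressed, and MANOVA on all research data nominally includes the staff scores. What remains could be detail that a condensed article leaves to the full protocol or analysis plan.

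Part of this stands. It cannot be said that research question 2 goes unanalysed. Nor is it contradictory in itself for staff knowledge to be an outcome in one analysis and a predictor of oral hygiene in another.

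A reader might also infer a much larger error: copy each home's staff score to its 30 residents, test 720 rows, and the false-positive rate is about 72% (Deff = 30 when ρ = 1). The documents do not support that reading. No section prescribes the copying, and ignoring the home level would go against the stated intention to handle clustering.

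The defence does not remove the conflict. The article is not silent on units: it names residents and defines the intraclass correlation of each outcome among them. The only clustering it describes is of residents within homes and homes within countries. The MANOVA sentence supplies neither the staff unit nor the staff clustering that a valid test needs.

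**Conclusion.** The point holds as a conflict over the unit of analysis for the staff outcomes. The stated methods do not give a valid test of research question 2, or of the part of research question 3 that depends on it. If staff were analysed individually with no cluster adjustment, the nominal 5% error would become about 10% to 32%, on the assumed 10 to 30 staff per home and staff intraclass correlation of 0.05 to 0.10. This is conditional on that analysis being run; it is not a forecast.

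A reader might extend the point to the primary outcome. That would be wrong: residents within homes is a coherent structure for plaque, and this unit conflict does not touch it. The matter is of moderate weight and should be settled before the staff data are analysed.

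**What to change.** - State that the resident and institution structure applies to the plaque outcomes only.
- Analyse knowledge and attitude with staff at level 1 and homes at level 2, with fixed terms for arm, country and arm by country. Alternatively, compare the 24 home means, adjusted for baseline home mean and country. Use small-sample degrees of freedom in either case.
- Define and report the intraclass correlation of these outcomes among staff within homes.
- If staff characteristics are used in the resident model, enter baseline values as home averages, not as individual-level covariates. Staff scores at 6 months are measured after randomisation, and adjusting for them could remove part of the intervention effect on oral hygiene.

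The cost is a change of wording and one extra model on data already due to be collected. Intervals for the staff outcomes will be wider, because they rest on 24 homes.

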## Methods/Design

### Design of the study

The study is a cluster randomized intervention trial with an institution as the unit of randomization. A random sample of 12 (residential) care homes accommodating a total of 120-180 somatic as well as psycho-geriatric residents in The Netherlands as well as in Flanders (Belgium) are randomly allocated to an intervention or control group. Representative samples of 30 residents in each of the 24 (residential) care homes are monitored during a 6-months period. Research data are gathered at baseline and at 6 months after the start of the study. The study is supervised and monitored by 2 investigators, the first and second author of this article. In each institution, an institution study supervisor, appointed by the managing director, is responsible for executing all study activities. The intervention consists of supervised implementation of the guideline "*Oral health care (residential) care homes for elderly people*" and a daily oral health care protocol. This protocol is derived from the guideline and formulated by the authors. Primary outcome variable is the oral hygiene level of the participating residents. To determine the stimulating or inhibiting factors of the implementation project and the nurses' and nurse aides' compliance and perceived barriers, a process evaluation is carried out [49]. The study is conducted according to the principles of the Declaration of Helsinki (version 17c, 2004) and in accordance with the Medical Research Involving Human Subjects Act (WMO). The study protocol is approved by the Ethics Committees of the Ghent University, Belgium (OG017 - approval 2008/440) and the Radboud University Nijmegen, The Netherlands (NL24666.091.08 approval 2008/273).

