### Participants and setting

In each country, a sample of (residential) care homes for elderly people is obtained using stratified (geographical distribution) cluster sampling with replacement. A (residential) care home is considered eligible for inclusion unless any of the following exclusion criteria are applicable:

• The management of the institution does not agree with the random allocation to the intervention or control group;

• The institution has mainly wards accommodating less than 20 residents;

• The institution has only somatic or psycho-geriatric wards;

• An oral health care guideline or protocol has already been introduced and implemented;

• Nurses and nurse aides have received special training on oral health care during the last 24 months;

• More than 5 other major care innovation projects have been implemented during the last 24 months.

Once the managing director of an institution agrees to participate by written informed consent, the institution is randomly allocated to either the intervention group or the control group of the country. Based on the power calculation (see following indentation) a representative cohort of 30 residents of the institution needs to be included.

Crucial factors for calculating the sample size (n) are the presumed distribution of the outcome measure (oral hygiene level) in the population of residents (*σ*), the presumed effect of the intervention (*μ*^1 ^- *μ*^2^), the power required (1-*β*), the a priori determined level of significance (*α*), and the value of the intraclass correlation (design effect). An a priori power of 80% and a level of significance of 0.05 are predetermined. The design effect (Deff) represents the ratio of the number of residents required using cluster randomization to the number of residents required using individual randomization.

The primary formula for calculating the sample size is: .

Deff = 1 + [(m - 1) *ρ*]; m = the number of residents in each institution, *ρ *= the intraclass correlation coefficient.

The adjusted sample size (n^adj^) equals: n × Deff. The number of residents in each institution (m) = n^adj ^: k; k = the number of institutions in the sample.

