Based on previous studies, an intraclass correlation coefficient of 0.95 and a standard deviation (sd) for dental plaque and denture plaque of 0.75 and 0.88 respectively is used. A 25% improvement of oral hygiene level is the presumed effect of the intervention. With regard to the design effect and drop-outs, loss to follow up, and uncertainty in power calculation, a sample size of 360 residents and 12 clusters per country seems an achievable number for the 6-months period. This means 30 residents per (residential) care home.

To participate in the study, a resident should:

• Supply a written informed consent, undersigned by himself or his legal representative

• Have teeth and/or partial or complete dentures

• Have the cognitive and physical condition required for undergoing an oral examination

• Be residing in the institution during the entire 6-months period presumably.

Residents are excluded when in day-care, in short-term residency, in coma, in palliative care or terminally ill, using a denture adhesive, expressing verbal or physical resistiveness before or during an oral examination.

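### Country is a third model level with only two units, so its variance and ICC are uninformative, and no arm-by-country contrast is named for research question 3

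*Protocol article*

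**What the plan says.** All places are in the protocol article.

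- **Model.** Under Statistical analysis, "a three-level structure is used with resident (level 1) and institution (level 2), nested in broader organization units on country level (level 3").
- **ICC.** The same section plans to calculate the intraclass correlation for each outcome "as a measure of correlation among residents within the institutions as well as among institutions within each country".
- **Contrasts.** It says that the effect of the project is analysed for individuals, institutions and countries. The comparisons it then lists are intervention against control and country against country, at baseline and at 6 months. No arm-by-country term is named.
- **Question to be answered.** Research question 3 (Aim and objectives) asks whether the impact on the outcomes of questions 1 and 2 differs between The Netherlands and Flanders, and "which factors are causing the country differences". The Discussion also refers to explanatory variables at country level.
- **Design.** Homes "in The Netherlands as well as in Flanders (Belgium) are randomly allocated to an intervention or control group" (Design of the study). Under Participants and setting, "the institution is randomly allocated to either the intervention group or the control group of the country". The numbers are 12 homes and 360 residents per country, 24 homes in all, with 30 residents in each.

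**The concern.** Two things do not fit together.

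First, a level in a multilevel model earns its place by having enough units to estimate a variance. Here the top level has two. They are also not a sample of countries: they are the two chosen settings within which homes are sampled and allocated. An ICC among institutions within a country needs a between-country variance, and two countries give almost no information about one.

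Second, a difference in impact between countries is an arm-by-country interaction. A variance of country intercepts, or a difference in mean plaque score between countries, describes how the countries differ in level. It does not say whether supervised implementation works better in one than in the other.

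At stake are the country-level quantities and the answer to research question 3. A zero country variance could be read as evidence that the countries are alike, and a country difference in plaque level could be reported as a difference in effect. Naming its causes would go a step beyond what two countries can show.

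**Working it through.** The plan gives no figure on this point, so there is none to reproduce. The layout is consistent: 12 homes × 30 residents = 360 per country, and 24 × 30 = 720 in all.

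**Inputs from the article:** 2 countries, 12 homes per country, 30 residents per home, SD 0.75 for dental plaque, ICC 0.95, significance level 0.05, power 80%.

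**Assumptions:** 6 homes per arm in each country (the article does not give the split), two-sided testing, equal variances, no drop-out. A home ICC of 0.05 is used beside the stated 0.95 to show a range.

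**1. Information on the country variance.** In a balanced nested analysis of variance with arm as a fixed effect, country has 2 − 1 = 1 df and homes have 24 − 3 = 21 df. An idealised 95% chi-square interval for each mean square is:

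- country, 1 df: 1/5.024 = 0.20 to 1/0.00098 ≈ 1018 times the observed mean square, an upper-to-lower ratio of about 5100;
- homes, 21 df: 0.59 to 2.04 times, a ratio of about 3.5.

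These multipliers belong to the between-country mean square. They are not limits for the country SD, because the variance component is that mean square minus the home mean square, divided by the group size.

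**2. How often the country variance is estimated as zero.** With variance of a home mean v = σ²(home) + σ²(resident)/30, the estimate is zero or negative when the F ratio of country to home mean squares is at most 1. The probability is P[F(1, 21) ≤ v / (v + 12 σ²(country))].

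| True country variance ÷ home variance | ICC 0.05 | ICC 0.95 |
|---|---|---|
| 0 | 67% | 67% |
| 0.1 | 54% | 49% |
| 0.5 | 35% | 29% |
| 1 | 27% | 22% |

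Example, ICC 0.05 and ratio 1, with total variance scaled to 1: v = 0.05 + 0.95/30 = 0.0817; 0.0817/(0.0817 + 12 × 0.05) = 0.120; probability 0.267.

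**3. The contrast that research question 3 needs.** With V the variance of a home mean on the plaque scale:

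- pooled arm effect, 12 against 12 homes: SE = √(2V/12);
- interaction, the difference of two arm effects each from 6 against 6 homes: SE = √(4V/6);
- ratio = √[(4/6)/(2/12)] = √4 = 2.

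As a fixed effect, the interaction has 24 homes − 4 cells = 20 df (critical t 2.09). If the arm effect were instead given a random slope over two countries, there would be 1 df (critical t 12.71).

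**4. What the interaction can detect (dental plaque, SD 0.75).**

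- ICC 0.05: V = 0.5625 × (0.05 + 0.95/30) = 0.0459; SE = 0.175; detectable at 80% power, 0.52 points.
- ICC 0.95: V = 0.5625 × (0.95 + 0.05/30) = 0.535; SE = 0.597; detectable at 80% power, 1.76 points on the 0–3 index.

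If the pooled arm effect had exactly 80% power, an interaction of the same size would have power Φ[(1.96 + 0.84)/2 − 1.96] = Φ(−0.56) ≈ 29%.

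**5. Causes of a country difference.** A country-level variable takes one value per country. With two countries it is an exact function of the country indicator, so no model can separate the two.

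**The case against.** The case on the other side has several parts.

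- **The plan does intend a country analysis of the effect.** This stands. A reader might infer that research question 3 is ignored; the text does not support that. What can be said is that the named contrasts contain no arm-by-country term, and that the mechanism offered, a third level, does not supply one.
- **Country is never called random.** Also true. It is an inference, but a reasonable one, since an ICC among institutions within a country requires a country variance component.
- **Exact model terms are commonly left to an analysis plan that is not shown.** That excuses the silence on the interaction term taken alone. It does not excuse the three-level structure and the country ICC, which the article states and which a later plan would have to reverse.
- **The variance can be computed.** Yes. A reader might conclude that it is inestimable; it is estimable on 1 df, which makes it uninformative.
- **The primary comparison is not harmed.** Largely right. A reader might fear for the arm effect and its standard error. Homes are allocated within country, so with balanced arms a country intercept cancels from the arm contrast, and no random country slope is stated.
- **Factors behind country differences can be studied.** In part. Table 1 collects institution, nurse and resident variables that vary within country and, with the process evaluation, can help describe differences. The limit applies to country-level factors and to the word causing.
- **A doubled standard error is generic.** True of any interaction over two equal strata. It is no error in the plan, but it is a limit to state when the result is reported.

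**Conclusion.** The point holds for the country-level quantities and for research question 3. With two countries, the country variance and ICC rest on 1 df. The variance would be estimated as zero or negative in roughly a fifth to two thirds of trials over the range examined. Neither that variance nor a country difference in plaque level tests the difference in impact that the question asks about.

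The correct contrast is available from the same data on about 20 df, but it is imprecise: twice the standard error of the pooled arm effect, and about 29% power for an interaction as large as a main effect that has 80% power. The figures assume 6 homes per arm per country, equal variances and two-sided testing; the detectable differences depend strongly on the ICC.

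The answer to research question 1 is little affected if allocation is balanced within country.

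**What to change.** 1. Replace the three-level structure by a two-level model: residents within homes, home random, with fixed effects for arm, country and arm-by-country.
2. Answer research question 3 with the interaction estimate and its 95% CI, tested against between-home variation on about 20 df (24 homes in 4 cells). Apply the same contrast to the nurse and nurse aide outcomes that the question also covers.
3. State beside the result that its standard error is about twice that of the pooled arm effect under balanced allocation, so a non-significant interaction is not evidence of equal impact.
4. Drop the country-level ICC and keep the ICC among residents within homes.
5. Reword the second half of research question 3 so that factors accompanying country differences are described, not called causes.

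The cost is analysis wording only. No data, homes or residents are added, and the design does not change. What is given up is a country variance that could not have been informative.
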